**Figure 1 F1:**
[figure not shown]
Study design flow-chart.

### Data collection and measures

#### Procedure

Each day, the cardiac nurse and the physiotherapist will check the bed list of patients admitted to the Cardiology Department. They will select the eligible patients after assessing the clinical history and consulting the cardiologist. In the inpatient setting, the cardiac nurse or the physiotherapist will give verbal and written information related to the study to eligible patients and will resolve all the patients’ doubts. These professionals will stress to the patient that the randomization process will decide the group inclusion. Before discharge (visit −1), eligible patients who agree to participate will be asked to give signed informed consent. In this visit, the cardiac nurse will record the following variables: education level, marital status, living situation, employment status and comorbidities (Charlson Comorbidity Index). On discharge (visit 0) the cardiac nurse or the physiotherapist will contact the Clinical Research Unit regarding the randomization process. Once the cardiac nurse or the physiotherapist knows the randomization group, they schedule the patient for the first cardiac nurse visit and for the exercise stress test.

Patients will attend four cardiac nurse visits (visits 1, 2, 3 and 4). During these visits, the cardiac nurse will describe ways of improving cardiovascular risk factors and cardiac medication adherence, and will answer the patients’ questions. The following variables will be recorded: attendance, systolic blood pressure (SBP), diastolic blood pressure (DBP), heart rate, Body Mass Index (BMI), abdominal circumference, Mediterranean diet, depressive symptoms (Yesavage Geriatric Depression Scale), basic activities of daily living (Barthel index), tobacco dependence (Fargeström test), compliance with cardiac medication (Haynes-Sackett test), taking sublingual nitroglycerin, hospital emergency visits, hospital readmissions and mortality. Quality of life (EuroQol5) will be recorded at all visits except visit 3. To address a possible cross-over effect, all patients will be asked to complete a physical activity questionnaire (Capersen and Powell classification) at baseline and in each follow-up visit. This test categorizes physical activity in four levels: sedentary, irregular activity, non-intensive regular activity, and intensive regular activity.

Further, during visit 1, the cardiac nurse will also record the diagnostic reason for referral (MI: location, severity, number of stents, ejection fraction), medication prescribed and level of risk for cardiac rehabilitation. At visit 4, the cardiac nurse will assess whether the patient can return to work. Patients will be administered a satisfaction survey with questions selected from the local public health department’s satisfaction questionnaire.

Blood tests will be performed at visits 1, 2 and 4. The following parameters will be determined: hemoglobin, leucocytes, platelets, urea, creatinine, sodium, potassium, cholesterol, high density lipoprotein cholesterol, low density lipoprotein cholesterol, triglycerides, creatine kinase-MB (CK-MB), C-reactive protein, glycosylated hemoglobin A1c (HbA1c), N-terminal Pro-B-type natriuretic peptide (NTproBNP), microalbumin and calcidiol.

The patient will do the exercise stress test at visit 1 and 2, under the guidance of the cardiologist and the nurse. The Bruce protocol stress test will be used. Before starting, the staff will describe the test to the patient and give some recommendations such as taking a light meal three hours before the test, avoiding stimulating drinks, taking prescribed medication and wearing comfortable shoes and clothes. In this protocol, exercise is performed on a treadmill (QUINTON® Q-STRESS TM 55). The leads of the ECG are placed on the chest wall. The treadmill is started at 2.74 km/hr (1.7 mph) and at a gradient (or incline) of 10%. At three minute intervals the incline of the treadmill increases by 2%, and the speed increases progressively. The exercise stress test will be limited by clinical signs such as arrhythmias and/or ECG changes and clinical symptoms such as general exhaustion, claudication of the legs, chest pain or dyspnea [13].

The following exercise stress variables will be recorded: theoretical maximum heart rate, real maximum heart rate, baseline heart rate, chronotropic index, the level reached on the exercise stress test, and time to recover initial heart rate (1 and 3 minutes). The cardiac nurse will collect blood before and after the exercise stress test in order to determine the level of troponin I.

Additional information will be recorded in the intervention group. Between visits 1 and 2, intervention patients will attend the training sessions. All sessions will be supervised by the physiotherapist. In each session the following values will be compiled: heart rate (initial, maximum, final), oxygen saturation (initial, during session, final), SBP (start, during session, final), DBP (initial, during session, final), degree of dyspnea (initial, final) and the level on the Borg scale. For each patient, the physiotherapist will compile the data from the exercise sessions and the number of physical sessions attended.

The cardiac nurse or physiotherapist will record the cause of withdrawal during the follow-up. The cardiac nurse will collect all data and enter them in a database designed for this study.

Table 1 summarizes the measures and variables according to the timeline.

**Table 1 T1:** Summary of measures and variables according to the timeline

**VISIT**	**−1**	**0**	**1**	**2**	**3**	**4**
**Time (months)**	**−1**	**0**	**1**	**3**	**6**	**12**
**Inclusion/exclusion criteria and informed consent**	X					
**Sociodemographic data** (sex, age, education level, marital status, living situation, employment status) and **comorbidity** (Charlson Index))	X					
**Cardiovascular risk factors** (diet, alcohol, tobacco dependence - Fargeström test - hypertension, diabetes, exercise practice, family heart disease), **dyspnea**, **depressive symptoms** (Yesavage Depression Scale) and **activities of daily living** (Bartel Index)	X		X	X	X	X
**Random allocation**		X				
**Diagnostic reason for referral** (localization, severity, number of stents, ejection fraction)			X			
**Medication prescribed**			X			
**Exercise stress test** (theoretical maximum heart rate, real maximum heart rate, baseline heart rate, chronotropic index, level reached, recovery time of the initial heart rate - 1 and 3 minutes-)			X	X		
**Level of risk for cardiac rehabilitation**			X			
**Control blood test**			X	X		X
**Anthropometric measures** (Body Mass Index, abdominal circumference)			X	X	X	X
**Systolic and diastolic blood pressure** and **baseline heart rate**			X	X	X	X
**Physical activity** (Capersen and Powell classification)			X	X	X	X
**Quality of life** (EuroQol5)			X	X		X
**Cardiac medication adherence** (Haynes-Sackett method) and **taking sublingual nitroglycerin**			X	X	X	X
**Adherence to Cardiac Rehabilitation Program**			X	X	X	X
**Hospital emergencies visits, number of readmissions and total days of hospitalization**			X	X	X	X
**Mortality**			X	X	X	X
**Cause of withdrawal**			X	X	X	X
**Return to work**						X
**Satisfaction with Cardiac Rehabilitation Program** (satisfaction questionnaire of the local public health department)						X

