#### Intervention

In addition to the usual hospital care, patients randomized to the intervention group will be provided with a supervised outpatient exercise training program, according to the results of the exercise stress test performed one month after hospital discharge and bearing in mind the physical limitations imposed by co-morbid conditions. The program will be performed in the hospital and it will start within the three days after the exercise stress test. It will comprise three hours a week (spread over three alternate days) of supervised exercise training for 10 weeks. The intervention will end after 10 weeks, regardless of whether the patients have completed 30 sessions. Exercise classes will be supervised by a physiotherapist and will consist of 10 minutes of warm-up and muscle stretching, 30 minutes of aerobic exercises (cycloergometer), 15 minutes of isotonic exercises for the upper and lower extremities and 5 minutes of cool-down. Moreover, instructions will be given on self-pulse counting, subjective perception of effort using the Borg scale, relaxation exercises, breathing techniques, postural health and minimizing physical effort. Aerobic exercise intensity will be between 75-90% of the maximum heart rate obtained in the previous exercise stress test and progressing according to the rating of perceived exertion (RPE: Borg scale 11–15). Resistance training will be performed with 10–15 repetitions for three sets, maintaining an RPE of 11–14. The physiotherapist will check that patients are exercising at their prescribed intensity with a pulse oximeter (Quirumed® Health & Care).

After hospital discharge, patients in both groups will have scheduled follow-up visits with a cardiac nurse at the first month, and then after 3, 6 and 12 months (visits 1, 2, 3 and 4 respectively) since hospital discharge in order to control the risk factors, reinforce education for disease control and review adherence to cardiac medication and CRP follow-up.

Control patients will be asked to complete the same outcome measures as the intervention group (See Figure 1).

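### At the stated times the 10-week programme ends 9 to 12 days after visit 2, so the only follow-up stress test falls before training is complete

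*Protocol article*

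**What the plan says.** All references are to the protocol article.

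- **Start of training.** The Intervention section says the programme is set "according to the results of the exercise stress test performed one month after hospital discharge" and that "it will start within the three days after the exercise stress test".
- **Length.** The same section gives "three hours a week (spread over three alternate days) of supervised exercise training for 10 weeks" and makes the end fixed: "The intervention will end after 10 weeks, regardless of whether the patients have completed 30 sessions".
- **Visits.** Both groups are seen by the cardiac nurse "at the first month, and then after 3, 6 and 12 months (visits 1, 2, 3 and 4 respectively) since hospital discharge". Table 1 repeats months 1 and 3 for visits 1 and 2.
- **Order.** The Procedure section states "Between visits 1 and 2, intervention patients will attend the training sessions".
- **Stress test.** The Procedure section states "The patient will do the exercise stress test at visit 1 and 2", and Table 1 marks no other occasion. The Abstract places the two tests in the first and third months after discharge.
- **Other visit 2 measures.** EuroQol and the control blood test are taken at visits 1, 2 and 4.

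Functional capacity, measured by the stress test, is a listed secondary outcome and part of the secondary hypothesis in the Background.

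**The concern.** The Procedure section treats visit 2 as the assessment that follows training. The stated dates put it before training can finish. Staff cannot follow all of these statements and must break one.

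If they keep month 3, the only follow-up of functional capacity is taken before the programme ends, and no later stress test exists to show the completed effect. If they instead wait until each intervention patient has finished, but see controls at month 3, the arms are tested at different times since discharge. Any difference in functional capacity would then mix the effect of training with a little extra recovery time. The trial is open, and the staff who book visit 1 and the stress test know the allocation, so such a drift is possible, though nothing in the text provides for it.

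**Working it through.** **The plan's own figure.** 3 sessions a week × 10 weeks = 30 sessions, as the Intervention section states.

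**Inputs.** Visit 1 and the stress test at month 1; start lag 0 to 3 days; programme 10 weeks = 70 days; visit 2 at month 3. The only assumption is the length of a month, taken first as 365.25 / 12 = 30.44 days.

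**Time available**
- Visit 1: day 30.4. Visit 2: 3 × 30.44 = day 91.3.
- Gap: 91.3 − 30.4 = 60.9 days = 8.7 weeks.

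**Time needed**
- 70 + 0 = 70 days to 70 + 3 = 73 days.

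**End of programme and overrun**
- No lag: 30.4 + 70 = day 100.4, and 100.4 − 91.3 = 9.1 days after visit 2.
- Three-day lag: 30.4 + 73 = day 103.4, and 103.4 − 91.3 = 12.1 days after visit 2.

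**Sessions possible by visit 2, with full attendance**
- No lag: 60.9 / 7 = 8.70 weeks; 3 × 8.70 = 26.1 sessions (87% of 30).
- Three-day lag: 57.9 / 7 = 8.27 weeks; 3 × 8.27 = 24.8 sessions (83% of 30).

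So about 25 to 26 of 30 sessions can have been given, and 4 to 5 remain.

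**Sensitivity to the month convention**

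| Month length | Gap, visit 1 to 2 (days) | Overrun, lag 0 to 3 days |
|---|---|---|
| 28 days | 56 | 14 to 17 days |
| 30 days | 60 | 10 to 13 days |
| 30.44 days | 60.9 | 9.1 to 12.1 days |
| 31 days | 62 | 8 to 11 days |
| Real calendar months | 59 to 62 | 8 to 14 days (70 − 62 to 73 − 59) |

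No convention removes the overrun.

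**Does the Abstract's looser timing help?** To finish by day 91.3, the first stress test would have to be done by day 91.3 − 73 = 18.3 (three-day lag) or 91.3 − 70 = 21.3 (no lag). A test on day 18 to 21 lies within the first month, but it conflicts with the Intervention section, which puts the test one month after discharge.

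**Which outcomes are exposed**
- Stress test: visits 1 and 2 only, so no measurement is scheduled after the programme ends.
- EuroQol and blood tests: repeated at month 12, so only the visit 2 value falls during training.
- Readmission outcomes and the sample size: counted over 12 months from discharge, so they do not depend on the date of visit 2.

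**The case against.** The strongest reply is that this is a matter of nominal labels. Visits are named in whole months, an overrun of 9 to 12 days is the size of an ordinary visit window, and windows are commonly left to a full protocol that is not shown. The Procedure sentence also makes the intended order clear: training first, visit 2 afterwards. This stands in part. The absence of a window is no fault in an article, and the text does not show a plan to assess patients during treatment. But a window would resolve the conflict only if it let visit 2 fall 9 to 12 days late, and the times that are stated still contradict each other.

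Three stronger readings are tempting, and the documents do not support them.

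- **That functional capacity and quality of life are measured in the middle of treatment.** At visit 2 some 83% to 87% of the programme can have been given, and EuroQol is taken again at month 12.
- **That the training effect will be understated by a material amount.** The article gives no relation between number of sessions and stress-test result, so the effect of the last 4 to 5 sessions is unknown. A modest understatement is possible, but its size is not shown.
- **That the arms will be assessed at different times.** The Intervention section puts both groups on the same clock from discharge. Unequal timing is a risk if staff improvise, not something the plan sets.

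It is also fair to say that functional capacity is one of many secondary outcomes and carries no power claim.

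**Conclusion.** The inconsistency is real. A fixed 10-week programme that starts after a month-1 stress test does not fit before a month-3 visit: 70 to 73 days are needed and about 61 are available. The programme ends 9 to 12 days after visit 2 with average months, and 8 to 17 days after it across the conventions tried. The result rests only on times stated in the article and on the length of a month.

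The consequence is confined to visit 2 and matters most for functional capacity, whose only follow-up comes with about 25 to 26 of 30 sessions deliverable. That may modestly understate the end-of-programme contrast, or leave the arms unequally timed if visit 2 is delayed in one arm only. Severity is moderate to minor: the schedule cannot be carried out as written, but it does not threaten the main conclusion of the trial.

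**What to change.** Reconcile the Abstract, the Intervention section, the Procedure section and Table 1 so that the start of training, its length and the date of visit 2 can all hold. The length of the programme is for the clinical team, and no change to it is proposed here.

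Whatever length is kept, set the visit 2 stress test, with the other visit 2 assessments, at one common interval from the visit 1 stress test. The interval should be identical in both arms and fall after the last possible training day. On the times now stated, that day is up to 73 days after the visit 1 stress test, against a gap of about 61 days, so visit 2 would move by about 73 − 60.9 = 12 days.

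The cost is a change of wording and an appointment moved by under two weeks in both arms. If recruitment has already started, the outcome will contain a mix of old and new visit 2 timing. That mix should be similar in the two arms if the change applies to both from the same date, and it should be reported.

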### Assessment of outcomes

#### Primary outcome measures

The primary outcome measures will be the percentage of patients readmitted, total number of readmissions and length of hospitalization for cardiac disease during the first year after hospital discharge and time to first hospital readmission for cardiac disease. The primary outcome will be assessed by an expert committee blind to the patient’s treatment group.

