### Statistical issues

#### Sample size

To ensure a statistical power of 80% in order to detect differences in the contrast of the null hypothesis (H_0_: equal percentages of cardiac readmissions in the two groups) through a two-tailed chi-square test for two independent samples, with a level of significance of 0.05, and assuming that the percentage of cardiac readmissions in the control group is 25% and the percentage in the intervention group is 12%, each group will require 139 patients. Assuming a 5% loss to follow-up, we estimate that 146 patients will be needed in each arm.

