#### Statistical analysis

Continuous variables will be summarized using means and standard deviations for normal distributions, and by medians and the 25th and 75th percentiles for non-normal distributions. Categorical variables will be summarized using absolute values and relative frequency. We will test for significant differences among the baseline characteristics of the control and intervention groups. For continuous variables, we will use the Student's *t*-test if both sample groups have normal distribution or the Mann–Whitney *U* test otherwise. We will use the *χ*^2^ test to compare categorical variables (or Fisher’s exact test in 2×2 contingency tables where the expected frequencies are lower than 5).

Percentage of patients readmitted for cardiac disease will be analysed through a two-tailed *χ*^2^ test for two independent samples, and time to first hospital readmission for cardiac disease will be analysed as time to event with Kaplan-Meier estimation and Cox proportional regression models. The deaths occurring without hospitalization will be introduced in the survival analysis as censored data. Event or censored times for all patients will be measured from the time of randomization (visit 0). All information available on the primary and secondary end points will be collected until the time of final contact with the patient, including patients lost to follow-up, at which point follow-up will be censored. Survival data will be presented graphically using the Kaplan-Meier method. We will use the log-rank test to compare the survival curves. To estimate the effect size, we will report the unadjusted hazard ratios (HR) and associated 95% confidence intervals (95% CI) obtained in the bivariate Cox proportional regression models.

To establish whether the allocation group is an independent prognostic factor for cardiac readmission, we will adjust for potential confounders in a multivariate analysis. The model will be adjusted with the significant covariates in bivariate analysis or those that were clinically significant. To estimate the effect size, we will report the adjusted hazard ratios (HR) and associated 95% confidence intervals (95% CI) obtained in the multivariate Cox proportional regression models.

Outcomes will be analysed on an intention-to-treat basis. A two-sided α-level of 0.05 will be considered statistically significant. Data will be analysed using IBM SPSS Statistics for Windows v.20 and Stata v.10.

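### Four overlapping cardiac-readmission measures are all called primary, with no ranking or success rule, although the trial is sized for only one of them

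*Protocol article*

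**What the plan says.** Under Primary outcome measures, the protocol article says: "The primary outcome measures will be the percentage of patients readmitted, total number of readmissions and length of hospitalization for cardiac disease", continuing "during the first year after hospital discharge and time to first hospital readmission for cardiac disease". The Abstract gives the same four. Neither place ranks them. The next sentence under Primary outcome measures speaks of a single primary outcome, to be judged by a blinded committee, without saying which of the four is meant.

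The Statistical analysis section sets one level: "A two-sided α-level of 0.05 will be considered statistically significant". It names a chi-square test for the percentage readmitted, and Kaplan-Meier, log-rank and Cox methods for time to first readmission.

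The Sample size section states one null hypothesis, "equal percentages of cardiac readmissions in the two groups", to be tested "through a two-tailed chi-square test for two independent samples, with a level of significance of 0.05". Its assumed rates and the resulting size read: "the percentage of cardiac readmissions in the control group is 25% and the percentage in the intervention group is 12%, each group will require 139". The allowance for dropout comes next: "Assuming a 5% loss to follow-up, we estimate that 146 patients will be needed in each arm".

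The primary hypothesis at the end of the Background concerns the incidence of cardiac readmissions. That could be read as patients readmitted, number of readmissions or time to the first one.

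**The concern.** If four outcomes have equal primary standing, the reader needs to know what pattern of results supports the primary claim: one named outcome, all four, or any one with the level adjusted. The protocol gives none of these.

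Two things are at stake. First, the stated 0.05 is not guaranteed for the primary claim as a whole, because its true level depends on how the results are combined and on which tests are used for counts and days. Second, the four can disagree. A few patients with many or long admissions can drive total readmissions or days in hospital while the percentage readmitted hardly differs. The Discussion looks ahead to savings from fewer readmissions and shorter total hospitalization, so a result on days alone would have a ready use. No rule says whether it would make the trial positive.

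**Working it through.** **1. The plan's own figure.** Inputs from the Sample size section: 25% versus 12%, two-sided 0.05, power 80%. The mean proportion is (0.25 + 0.12)/2 = 0.185.

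n = [z(0.975)·√(2·0.185·0.815) + z(0.80)·√(0.25·0.75 + 0.12·0.88)]² / 0.13²
= [1.960·0.5491 + 0.8416·0.5414]² / 0.0169 = 138.9, so **139 per group**.

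The stated figure reproduces, with power 80.0%. The allowance for loss also agrees to within rounding: 139·1.05 = 145.95, and 139/0.95 = 146.3. The full 0.05 is spent on the percentage; nothing is held back for other outcomes.

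**2. Limits that ignore the overlap.**
- Four tests at 0.05: at most 4·0.05 = 20% under any dependence, and 1 − 0.95⁴ = 18.5% if independent.
- Two tests at 0.05: 1 − 0.95² = 9.75% if independent.

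These are reference values only. All four outcomes are built from the same readmissions, so independence is not plausible.

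**3. The two outcomes with named tests.** Chi-square plus log-rank, simulated with no treatment effect: 139 per arm, 18.5% readmitted, constant hazard, no loss, 20,000 replicates. The chance that at least one is significant was 5.2%. A separate simulation gave about 5-6%. There is almost no inflation here.

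**4. All four outcomes.** The tests for counts and days are not named, so several choices were tried. Assumptions: 139 per arm, no treatment effect, overdispersed (negative-binomial) counts and log-normal stays. The first two result columns use 6,000 replicates per row.

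| Readmitted | Dispersion parameter | Rank tests, all patients | t-tests on mean count and days |
|---|---|---|---|
| 25% | 0.5 | 6.5% | 9.9% |
| 25% | 2 | 6.6% | 9.8% |
| 18.5% | 0.5 | 5.2% | 9.0% |
| 18.5% | 2 | 5.8% | 8.7% |

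The simulation standard error near 6% is √(0.06·0.94/6000) = 0.3 percentage points, so the lowest rank-test figure cannot be told apart from 5%. When stay is compared only among readmitted patients (4,000 replicates per setting), the family-wise error was 9.8-12.5%.

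The inflation therefore comes from the count and the days, and its size depends on how they are tested.

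**5. Power for the others.** None is stated. As an illustration for time to first readmission, a constant hazard gives HR = ln(0.88)/ln(0.75) = 0.444. The expected events are 139·(0.25 + 0.12) = 51, which gives power of about 83%. For counts and days the protocol gives no inputs.

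**6. Two ways to repair it.**
- One primary (the percentage) at 0.05: 139 per group, power 80.0%, no change.
- Four co-equal primaries with Bonferroni, 0.05/4 = 0.0125 each: the percentage alone needs 198 per group (198/0.95 = 208.4, so 209 with loss). At 139 per group its power falls to 61.7%.

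**The case against.** The strongest reply is that the deciding outcome is already clear. There is one primary hypothesis, one null hypothesis, and one sample size built on the percentage. The outcome analysis opens with that percentage and the same chi-square test, and the text once speaks of a single primary outcome. On this view the fault is loose labelling. Much of this stands: these places do point to the percentage, which is why the repair is simple. But they do not rank the outcomes, and the Abstract and Primary outcome measures give the other three equal standing.

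Three stronger readings are tempting, and the document does not support them:

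- *Any one of four significant results makes the trial positive.* No such rule is written. The protocol has no decision rule at all, which is a different fault.
- *The type I error is 18.5%.* That needs four independent tests. The outcomes share the same events, and the two with named tests barely inflate the error. The only rule given for non-normal continuous data is Mann-Whitney. It is stated for baseline comparisons, but if carried over to counts and days it gives only about 5-7%.
- *Four tests are specified, or two are wrongly omitted.* Tests are named for two outcomes. Leaving the other two to an analysis plan that is not shown is normal and no error.

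That analysis plan might also hold a testing order. This does not remove the point: the protocol itself fixes four co-equal primaries, so a later ranking would alter what it says.

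**Conclusion.** The point holds in a limited form. Four measures are primary without a ranking or a success rule, one flat 0.05 applies, and only the percentage readmitted was sized. The sample-size arithmetic is sound.

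The inflation ranges from almost none to about double the stated level. It is about 5-6% for the two outcomes with named tests, about 5-7% for all four with rank tests on all patients, and about 9-12% with mean-based tests or stay compared among readmitted patients. These figures apply if any single significant result is taken as success. They rest on assumed models for repeat admissions and length of stay, which the protocol does not supply.

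The lack of a rule for conflicting results depends on none of these assumptions. It is reason enough to correct the wording, as an inexpensive improvement that fixes what the trial can conclude.

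**What to change.** In the Abstract and under Primary outcome measures, name one primary outcome: the percentage of randomised patients with at least one cardiac readmission within 12 months of discharge. List time to first cardiac readmission, number of cardiac readmissions and days in hospital for cardiac disease as secondary. Alternatively, test those three in a fixed order, stated in advance, and only if the primary result is significant.

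Time to first readmission could also have been chosen to lead, since it handles censoring. The percentage is preferred because the null hypothesis and sample size are already written for it.

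The cost is wording in the protocol, with matching changes to the registry entry and analysis plan, made before outcome data are seen. The 139 per group (146 with loss) and 80% power do not change. The sponsor gives up the option of a primary claim on the other three outcomes.
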